### Exclusion criteria

ADPKD is accompanied by proteinuria (> 1 g/d)diabetic patientsunable to or do not consent to participate in the studysuffering from chronic hepatitis, drug-induced hepatic dysfunction, or another type of hepatic dysfunctionrecent participation in another clinical trialprobable, highly likely, or definite allergy to any of the ingredients in the test drugcontraindications to magnetic resonance imaging (MRI)taking medications likely to affect ADPKD outcomes

### Participant withdrawal criteria

Participants will be withdrawn from the study ifThey violate any of the key inclusion or exclusion criteria.They refuse to continue to participate or withdraw their consent.They undergo a serious adverse event (SAE).They have unbearable ADPKD-related pain and choose cyst decompression as a surgical intervention during the study.The principal investigator or co-investigators judge that they need to be withdrawn from the study.A hepatocellular injury is detected, indicated by alanine transaminase (ALT) or aspartate transaminase (AST) levels > 3 × ULN and total bilirubin > 2 × ULN, where ULN is the upper limit of normal.They have hematuria during treatment.

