### Measurement items and time points of data collection

Relevant examinations will be performed to collect patient data at 24 weeks before baseline, at baseline, every 4 weeks from 4 to 24 weeks during treatment, and an additional follow-up evaluation will be performed at visit 9 (48 weeks). General information collected will include name, age, gender, ID number, date of birth, home address, contact information, history of present illness, past medical history, family history, personal life history, menstrual history, marital history, allergy history, social history, physical examination results, and laboratory examination results.

There is evidence that age-related TKV can reflect the progress of ADPKD. An MRI scan can accurately measure renal blood flow and evaluate renal cyst compression, which is associated with pain, hypertension, hematuria, albuminuria, and loss of renal function. TKV combined with age and renal function can be used to evaluate the risk of progress to ESRD [19]. The T2 shortening imaging technique of MRI with no radiation damage, no use of gadolinium as a contrast agent, and no risk of nephrogenic systemic fibrosis is recommended and will be used in this study [20]. The outcome is the percentage semi-annual change in TKV measured by MRI, which will be performed at visit 1, visit 2 (24 weeks after visit 1), and visit 8 (24 weeks after visit 2) to observe the growth in kidney volume before and after the intervention.

Items to be measured and the time points of data collection are listed in Table 2.

**Table 2 Tab2:** SPIRIT table: Measurement items and time points of data capture

Items	Screening	Baseline	Treatment						Follow-up
	Visit 1	Visit 2	Visit 3	Visit 4	Visit 5	Visit 6	Visit 7	Visit 8	Visit 9
	−24 weeks	0 weeks	4 weeks	8 weeks	12 weeks	16 weeks	20 weeks	24 weeks	48 weeks
General									
Informed consent	×								
Inclusion and exclusion criteria	×								
Collect general information	×								
General physical examination	×								
Urine hCG (only women)	×								
Medical and drug use history	×								
Concomitant disease and treatment	×								
Combined medication	×	×	×	×	×	×	×	×	×
Effectiveness observation									
Vital signs	×	×	×	×	×	×	×	×	×
TCM symptoms	×	×	×	×	×	×	×	×	×
Pain evaluation	×	×	×	×	×	×	×	×	×
Renal function (eGFR, Scr, BUN)	×	×	×	×	×	×	×	×	×
MRI (TKV)	×	×						×	
Blood electrolytes	×	×			×			×	×
Urine β2-MG, mALB/Cr, RBP	×	×						×	×
Safety observation									
Blood test ^#^	×	×			×			×	×

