### Data and safety monitoring

An independent data and safety monitoring board comprising cardiovascular surgeons, anesthesiologists, and statisticians will oversee all aspects of the study. The board will meet twice during the trial to monitor safety. It will make recommendations on study progress and performance, identify any major adverse outcomes or AEs due to the therapy, and give advice regarding whether the study should continue or if there should be a protocol change.

In this study, AEs are defined as any negative or unintended clinical manifestations that occur after the start of the study, regardless of medication. Any unexpected symptoms and signs, feelings of discomfort, or occurrence of AEs in patients during the trial will be recorded using medical diagnostic terminology on a case report form with detailed symptoms, time of occurrence, duration, severity, possible causal relationships, actions taken, results, and other relevant information. If an AE occurs, the patient will be monitored until their AE disappears. A follow-up investigation will be conducted, and the results will be recorded in case the intervention is halted due to the AE. The chief principal investigator ([name]) is responsible for reporting all AEs to the board and the regulatory authorities within 24 h.

The following are possible safety events relating to the intervention:decrease of eGFR by ≥50%Scr doubled since the last blood testprogression to CKD stage Vserious cardiovascular or cerebrovascular eventsheart rate < 40 bpmany unexpected event that the investigator believes could be attributed to the intervention

SAEs include any of the following:fatal or life-threatening complicationsdeath or persistent or significant disabilityhospitalization or significant medical intervention to prevent a serious outcomeany events that investigators examine are significant hazards or harm to the participants

Stopping rules for the trial:If an insufficient number of patients is enrolled.If the allocation codes are leaked during the trial or if more than 20% of the envelopes with emergency plans are opened, which would mean that the blinding has been nullified.Occurrence of SAEs that are likely to be related to the intervention drugs in the trial, which may indicate there are serious problems with the safety of the drug.

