### Data entry and quality control of data

Participant adherence to the protocol will be monitored by interviews at study check-up visits, which will promote retention and completion of follow-up assessments.

After verification of the content of the written case report forms, the data will be input independently into a database by two full-time research staff. To maintain data quality, all investigators will receive centralized training before the trial begins. Personal information (such as name, age, gender, ID number, date of birth, home address, contact information) will be kept in a locked storage unit according to standard guidelines. The quality control of the data will be assessed by the data and safety monitoring board three times at each trial site. The board will check that study procedures have been followed correctly according to the approved protocol. They will compare the data in the database with the source documents to evaluate its accuracy, completeness, and authenticity. The data and safety monitoring board will meet when the first participant enrolls, when 50% of the participants have been recruited, and when the last participant enrolls.

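### Six non-consent events remove randomised patients from the study, not only from study drug, so week-24 eGFR and MRI that could be measured would be imputed

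*Protocol article*

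**What the plan says.** The Participant withdrawal criteria section opens with "Participants will be withdrawn from the study ifThey violate any of the key inclusion or exclusion criteria" and lists six further triggers. They include "They undergo a serious adverse event (SAE" and "They have hematuria during treatment". The section does not separate stopping the granules from leaving the trial.

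The Data and safety monitoring section defines serious events broadly: "SAEs include any of the following:fatal or life-threatening complicationsdeath or persistent or significant disabilityhospitalization or significant medical intervention". For adverse events it provides monitoring until the event resolves, and adds "A follow-up investigation will be conducted, and the results will be recorded in case the intervention is halted due to the AE". The data entry and quality control section says "Participant adherence to the protocol will be monitored by interviews at study check-up visits, which will promote retention and completion of follow-up assessments".

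Table 2 schedules renal function at all nine visits. MRI is limited to three scans, "which will be performed at visit 1, visit 2 (24 weeks after visit 1), and visit 8 (24 weeks after visit 2".

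The Statistical analysis section includes all enrolled patients in an intention-to-treat primary analysis and handles missing data by multiple imputation. The Sample size calculation section allows for 10% dropout.

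**The concern.** An intention-to-treat comparison needs outcomes from randomised patients whether or not they stay on drug. A rule that removes patients after randomisation for clinical events creates missing data that the trial could have avoided. The SAP cannot recover measurements that were never taken.

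Some of the triggers also lie close to the disease process. The protocol itself describes "renal cyst compression, which is associated with pain, hypertension, hematuria, albuminuria, and loss of renal function", and two triggers are hematuria and cyst decompression for pain. Patients lost this way may therefore differ in renal course from those who remain, and imputation would have to carry that difference. The most direct markers of renal decline among the listed safety events (a halving of eGFR, a doubling of creatinine, reaching CKD stage V) are not themselves named as withdrawal triggers, which limits how far this argument goes.

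**Working it through.** **1. Sort the triggers.** Seven are listed in Participant withdrawal criteria.

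- Consent-related (1): refusal or withdrawn consent.
- Not consent-related (6): entry-criterion violation; any serious adverse event; cyst decompression for pain; investigator judgement; hepatocellular injury; hematuria during treatment.

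The serious-event trigger does not require a link to study drug, and hospitalisation counts as serious. Hematuria has no grade or threshold, and Table 2 schedules a urine test at every visit.

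**2. Look for text that keeps outcome measurement going.**

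- Data and safety monitoring: follow-up of the adverse event. It names no eGFR, MRI or scheduled visit, and it does not reach entry violations, elective decompression or general investigator judgement.
- Data entry and quality control of data: a general statement on retention, not directed at withdrawn patients.
- Table 2: no entry for withdrawn patients.

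Nothing overrides the withdrawal rule. That measurement ends is its plain reading; the protocol does not say so in terms.

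**3. Count what a withdrawn patient loses (Table 2).** Post-baseline renal function: Visits 3 to 9 = 7. Post-baseline MRI: Visit 8 = 1.

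| Withdrawn just after | eGFR visits lost | Week-24 eGFR | Post-baseline MRI |
|---|---|---|---|
| Week 4 (Visit 3) | Visits 4–9: 6 of 7 | lost | 1 of 1 lost |
| Week 12 (Visit 5) | Visits 6–9: 4 of 7 | lost | 1 of 1 lost |
| Week 20 (Visit 7) | Visits 8–9: 2 of 7 | lost | 1 of 1 lost |

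For eGFR, imputation can use the earlier four-weekly values. For kidney volume it has only the two pre-treatment scans.

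**4. Reproduce the sample size.** Inputs from Sample size calculation: difference 6, SD 8.53, α = 0.05 (two-sided per Statistical analysis), power 0.80, ratio 1:1.

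n per arm = (1.960 + 0.842)² × 8.53² × 2 / 6² = 7.85 × 72.76 × 2 / 36 = 31.7, rounded up to 32; total 64. With 10% dropout, 64 / 0.9 = 71.1, rounded up to 72. The plan's figures reproduce.

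**5. Compare with the allowance.** 72 − 64 = 8 patients (8/72 = 11.1%), or 36 − 32 = 4 per arm. This must cover the six triggers as well as withdrawn consent. A fifth loss in one arm (5/36 = 13.9%) leaves 31, below 32.

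**6. Illustrate power on observed outcomes.** Power = Φ(6 / (8.53 × √(2/n)) − 1.960), with n observed per arm. The loss rates are assumptions, since the documents give none, and the figures ignore what imputation recovers from earlier visits.

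| Assumed loss | n per arm | Power |
|---|---|---|
| 0% | 36 | 0.847 |
| 10% | 32.4 | 0.808 |
| 15% | 30.6 | 0.786 |
| 20% | 28.8 | 0.761 |
| 30% | 25.2 | 0.704 |

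**The case against.** The strongest reply is that this is a condensed article. It says when patients are withdrawn, not that measurement stops, and off-treatment visits are the kind of detail left to a full protocol. The safety section does distinguish halting the intervention from ending observation, and serious events, liver injury and new hematuria could all fall under it. This makes a complete stop to data collection less than certain. It does not dispose of the point, because the article states a rule, withdrawal from the study, and the safety text names no efficacy measurement.

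Second, not every lost outcome could have been obtained. Outcomes after death cannot be measured, and kidney volume after decompression partly reflects the surgery. Entry violations found between Visit 1 and allocation at Visit 2 do not touch the randomised comparison. All of this stands, and the point is limited to randomised patients who can still be measured.

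Third, no effect is demonstrated. That also stands. Power changes little near the allowance (0.786 even at an assumed 15% loss), and earlier eGFR values support the imputation. The stronger reason to change the rule is that it discards outcomes from a non-random subset of patients.

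Fourth, it could be said that the remedy removes the investigator's discretion and burdens patients after serious events. Drug would still stop for safety, and a patient can decline further visits by withdrawing consent.

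**Conclusion.** The concern holds and should be fixed. Followed as written, the rule takes randomised patients out of the study for six reasons other than consent. Each patient withdrawn before week 24 then has no week-24 eGFR and no post-baseline kidney volume, although both visits are already scheduled. The intention-to-treat analysis would rest on imputed values where real ones could have been collected.

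The conclusion depends on reading withdrawal from the study as ending scheduled outcome collection; a fuller protocol could say otherwise. The size and direction of any bias, and any difference between arms, cannot be determined from the documents.

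A smaller point belongs with this one: hematuria during treatment triggers withdrawal, while the Intervention section lists drugs for hematuria among the basic therapy in both arms. The protocol does not say which hematuria falls under which rule.

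**What to change.** For randomised participants:

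- Make the six non-consent triggers reasons to stop study drug only. End follow-up only when consent is withdrawn.
- State that eGFR, serum creatinine, adverse events and the Visit 8 MRI are collected on schedule for everyone else.
- Analyse patients found after randomisation to violate an entry criterion in the arm to which they were allocated.
- Record the dates of drug stop and of any cyst decompression, so that the SAP can say how later values, kidney volume in particular, are used.
- State which hematuria stops study drug and which is treated as basic therapy.

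The cost is a protocol amendment. Ethics approval was given at each participating hospital, and Trial status has follow-up visits running from July 2019, so review at three sites is likely. Some patients would attend visits off drug. The eGFR visits and the Visit 8 MRI are already in the schedule, and the sample size stays at 72.

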Urine test	×	×	×	×	×	×	×	×	×
Stool routine and occult blood test	×	×			×			×	×
Liver function (ALT, AST, γ-GT)	×	×			×			×	×
Electrocardiogram	×	×						×	×
Other data									
Adverse events			×	×	×	×	×	×	
Allocation		×							
Drug distribution		×	×	×	×	×	×		
Drug recycling			×	×	×	×	×	×	
Drug count			×	×	×	×	×	×	
Research conclusion								×	×

Each visit allows a window of 3 days

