# The blood test assesses the red blood cell count, white blood cell count, hemoglobin level, and platelet level

*eGFR* estimated glomerular filtration rate, *hCG* human chorionic gonadotrophin, *Scr* serum creatinine, *BUN* blood urea nitrogen, *β2-MG* β2-microglobulin, *mALB/Cr* microalbumin/creatinine, *MRI* magnetic resonance imaging, *RBP* retinol-binding protein, *ALT* alanine aminotransaminase, *AST* aspartate aminotransaminase, *γ-GT* gamma glutamyl transpeptidase, *TCM* traditional Chinese medicine, *TKV* total kidney volume

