### Outcomes

The primary outcome of this trial will be the eGFR using the CKD Epidemiology Collaboration formula [21]. Secondary outcomes include changes in TKV, Scr, blood urea nitrogen (BUN), TCM symptoms, and pain. A composite outcome looks at the incidence rates of all possible safety events between two groups. AEs will be monitored throughout the trial and several biological indicators (blood and urine tests, electrocardiograms, and liver function test) will also be closely watched.

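### The liver-injury withdrawal criterion needs total bilirubin, but Table 2 schedules it at no visit, so the criterion cannot be evaluated from scheduled tests

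*Protocol article*

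**What the plan says.** The section Participant withdrawal criteria lists seven grounds for withdrawal. One is hepatocellular injury, shown by ALT or AST above a threshold together with total bilirubin above another: "levels > 3 × ULN and total bilirubin > 2 × ULN". The two parts are joined by a plain conjunction.

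Table 2, in the section Measurement items and time points of data collection, sets the tests for each visit. The liver row reads "Liver function (ALT, AST, γ-GT" with nothing further in the bracket, and it is marked at Visits 1, 2, 5, 8 and 9. A footnote to the table defines the blood test: "The blood test assesses the red blood cell count, white blood cell count, hemoglobin level, and platelet level".

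The Outcomes section says of safety laboratory data that "several biological indicators (blood and urine tests, electrocardiograms, and liver function test) will also be closely watched". It does not name bilirubin.

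**The concern.** A criterion with two necessary parts can be applied only if both are measured. Here the schedule provides the transaminases but not the bilirubin. A site that does exactly what Table 2 asks could see ALT or AST above its threshold and still be unable to say whether the participant meets the criterion.

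Two things are at stake. The first is participant protection: this is the only place in the article that sets numeric liver thresholds, in a trial of a 17-ingredient product taken for 24 weeks. The second is interpretation. If bilirubin is obtained only when a local physician asks for it, detection can differ between the three hospitals. A count of zero withdrawals for hepatocellular injury would then not separate an absence of injury from an absence of measurement.

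**Working it through.** No sample-size or error-rate formula applies. The check sets the criterion beside each source of scheduled laboratory data.

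**What the criterion needs** (Participant withdrawal criteria): (a) ALT or AST, and (b) total bilirubin. Both are necessary.

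**What the schedule supplies** (Table 2 and its footnote):

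| Table 2 item | Stated content | Supplies (a)? | Supplies (b)? |
|---|---|---|---|
| Liver function | ALT, AST, γ-GT | yes | no |
| Blood test | red cells, white cells, hemoglobin, platelets | no | no |
| Renal function | "Renal function (eGFR, Scr, BUN", closing the list | no | no |
| Blood electrolytes | electrolytes | no | no |
| Urine markers | β2-MG, mALB/Cr, RBP | no | no |
| Urine test, stool test | urine and stool | no | no serum value |

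Outside Participant withdrawal criteria, bilirubin is named nowhere in the article. It is absent from Outcomes, from Data and safety monitoring and from the abbreviation list.

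**Count by visit:**

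| Liver panel | Week | Position | (a) measured | (b) measured |
|---|---|---|---|---|
| Visit 1 | −24 | before treatment | yes | no |
| Visit 2 | 0 | baseline | yes | no |
| Visit 5 | 12 | during treatment | yes | no |
| Visit 8 | 24 | end of treatment | yes | no |
| Visit 9 | 48 | 24 weeks after treatment ends (48 − 24) | yes | no |

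Part (a) is available at 5 of 9 visits and part (b) at 0 of 9, so the joint criterion can be evaluated at 0 of 9 visits from scheduled tests.

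Not all five panels carry the same weight. Visits 1 and 2 precede dosing, and Visit 9 falls well after it. The panels that bear on treatment are the two at weeks 12 and 24. Week 24 is the end of treatment, so week 12 is the only panel at which the criterion could still interrupt dosing.

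**Is this just a shortened table?** Table 2 does not stop at a generic label such as liver function. It names the analytes, and a footnote does the same for the blood test. The liver list includes γ-GT, which the criterion does not use, and leaves out total bilirubin, which it does. So two explicit statements in the same article do not fit together.

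**The case against.** The strongest reply is that the criterion is not confined to scheduled tests. It speaks of injury being detected, and Data and safety monitoring requires adverse events to be recorded with the actions taken and followed until they resolve. A raised ALT or AST at a scheduled visit could lead a physician to order bilirubin, and that result would count. Separate grounds for withdrawal also exist: a serious adverse event, investigator judgement, and violation of key eligibility criteria, which include hepatic dysfunction. This stands. A reader might infer that the criterion can never operate, or that a participant with liver injury has no route out of the trial. The documents support neither inference. What they do not contain is any instruction to measure bilirubin when ALT or AST rises, so this route rests on local discretion.

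A second reply is that the criterion governs withdrawal and is not a reporting definition. This also stands. A reader might infer that liver safety cannot be reported. However, Outcomes and Data and safety monitoring define the safety events without using the joint criterion, and ALT, AST and γ-GT can be summarized in full.

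A third reply is that this is a journal article and the full protocol or case report form may include bilirubin. That is possible, so the finding is not that the trial never measures bilirubin. It is that the article's table and its criterion disagree. If bilirubin is in fact measured, Table 2 states the panel incompletely and still needs correcting.

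Finally, the mismatch does not touch the primary outcome, randomization, power or the analysis. That is true and limits its scope, but it is no reason to leave a safety criterion and its schedule at odds.

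**Conclusion.** The point holds as an internal inconsistency. On the schedule as written, the hepatocellular-injury criterion can be evaluated from scheduled tests at none of the nine visits, because total bilirubin is missing from all five liver panels, including those at weeks 12 and 24. The consequence is limited to this criterion: its detection would depend on unscheduled testing at each site, and an absence of withdrawals under it would be uninformative unless bilirubin is known to have been measured.

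This assumes that Table 2 lists the liver panel and the blood test completely, as its wording suggests. No event rate or estimate of harm is claimed, since the article gives none. No view is taken on whether the thresholds or the panel are the right ones.

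**What to change.** Reconcile Participant withdrawal criteria with Table 2 so that every analyte the criterion uses appears on the scheduled panel. If the criterion stands as written, that means listing total bilirubin with the liver function tests already drawn at Visits 1, 2, 5, 8 and 9, and providing for it on the case report form. If the full protocol already measures bilirubin, only the wording of Table 2 needs correcting. Any change to the criterion itself is a clinical decision for the clinical team and the monitoring board.

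The cost is at most one further analyte on blood that is already taken, plus wording in Table 2 and the case report form. No added visit, sample-size change or change to the analysis is needed.

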### Intervention

According to the guideline for the management of ADPKD [18], drugs used in the treatment of hypertension, hematuria, concurrent infections, and other diseases will be used reasonably for patients in both groups as basic therapy, except for Chinese patent drugs. The name and dosage of any drug administered will be recorded. In addition to their standardized Western medicine, participants randomized to the treatment group will be administered YNF as an oral dose of 36 g twice daily 1 h after breakfast and dinner for 24 weeks. Those in the control group will receive the placebo as an oral dose of 36 g twice daily 1 h after breakfast and dinner for 24 weeks. Both groups will receive behavioral intervention and health education, such as diet instructions. All co-investigators and patients will be educated about drug administration methods.

The YNF granules (10% YNF) and the placebo granules will be manufactured by Jiangsu Tianyin Pharmaceutical Co. Ltd. ([name]) according to good manufacturing practice. The composition and action of each herb are summarized in Table 1.

**Table 1 Tab1:** Composition and action of *yinang* formulation in Chinese herbal medicine

Ingredient	Granule dose	Action (TCM)	Pharmaceutical action
Rhizoma sparganii (*sanleng*)	10 g	1. Regulate qi 2. Relieve pain 3. Promote blood circulation 4. Alleviate stagnation	1. Inhibit platelet aggregation and thrombosis
Ranunculus ternatus Thunb (*maozhuacao*)	30 g	1. Dissipate phlegm 2. Dispel stasis 3. Detoxify 4. Detumescence	1. Anti-inflammation 2. Anti-tumor
Spina gleditsiae (*zaojiaoci*)	6 g	1. Detoxify 2. Disperse swelling	1. Anti-tumor
Rhizoma drynariae (*gusuibu*)	10 g	1. Reinforce the kidneys 2. Strengthen bones 3. Relieve pain	1. Prevent osteoporosis 2. Anti-inflammatory
Astragalus (*huangqi*)	30 g	1. Tonify qi 2. Diuresis	1. Improve the immune function 2. Anti-oxidant 3. Increase resistance to radiation 4. Anti-tumor
*Codonopsis pilosula* (*dangshen*)	30 g	1. Invigorate the spleen 2. Replenish qi	1. Regulate the central nervous system 2. Enhance immune function 3. Regulate gastrointestinal motility 4. Cardiovascular protective effect
Angelica sinensis (*danggui*)	10 g	1. Enrich the blood 2. Invigorate the circulation of blood	1. Anti-atherosclerosis 2. Bacteriostasis 3. Anti-hypoxia 4. Regulation of immune function 5. Inhibit platelet aggregation

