Paeoniae radix (*chishao*)	15 g	1. Activate blood circulation to dissipate blood stasis	1. Inhibition of platelet and erythrocyte aggregation 2. Anti-atherosclerosis 3. Anti-tumor 4. Protect the heart and liver 5. Anti-coagulation and anti-thrombosis
Radix paeoniae alba (*baishao*)	10 g	1. Nourish the blood 2. Reduce yin 3. Soothe the liver 4. Relieve pain 5. Stabilize yin and yang in the liver	1. Anti-inflammation 2. Pain relief 3. Liver protection
*Duchesnea indica* (*shemei*)	10 g	1. Clear away heat and toxic material 2. Activate blood circulation to dissipate blood stasis	1. Anti-oxidant
Hedyotis diffusa willd (*baihuasheshecao*)	15 g	1. Dissolve phlegm 2. Detoxification 3. Detumescence	1. Anti-inflammation 2. Anti-tumor 3. Regulation of immune function
Cowherb seed (*wangbuliuxing*)	15 g	1. Activate blood circulation to dredge collaterals 2. Detumescence 3. Relieve pain	1. Inhibit microcapillary proliferation 2. Inhibit migration and adhesion of endothelial cells
Semen brassicae (*baijiezi*)	15 g	1. Activate qi 2. Activate blood circulation 3. Dredge collaterals 4. Relieve pain	1. Anti-hepatic fibrosis 2. Regulation of TGF-β1/Smad, NF-κB, and AKT signaling pathways 3. Reduction of extracellular matrix deposition
Plantaginis seeds (*cheqianzi*)	15 g	1. Clear heat 2. Diuresis 3. Permeate dampness 4. Promote circulation 5. Clear eyesight 6. Expectorant	1. Eliminate oxygenic free radicals 2. Anti-oxidation in lipid metabolism 3. Anti-oxidation
*Polygonum cuspidatum* (*huzhang*)	10 g	1. Relieve coughing 2. Resolve phlegm 3. Dispel wind dampness 4. Remove fluid 5. Dissipate blood stasis 6. Relieve pain	1. Anti-bacterial and anti-viral 2. Protect the cardiovascular system 3. Anti-inflammation and analgesic 4. Liver protection 5. Enhance immunity 6. Anti-tumor
*Centella asiatica* (*jixuecao*)	30 g	1. Clear heat 2. Disperse dampness 3. Detoxify 4. Reduce swelling	1. Improve the microcirculation 2. Relieve pain 3. Anti-oxidant 4. Anti-bacterial 5. Anti-inflammation 6. Anti-fibrous tissue proliferation
Prepared rhubarb (*dahuang*)	10 g	1. Alleviate accumulation 2. Clear heat 3. Detoxify 4. Remove blood stasis 5. Dredge meridians	1. Promote defecation 2. Anti-bacterial 3. Protect the liver and gallbladder 4. Lower blood pressure 5. Lower blood lipid levels

*TCM* traditional Chinese medicine

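### Hematuria on treatment takes a patient out of the study, not just off study drug, so eGFR follow-up can end before week 24

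*Protocol article*

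**What the plan says.** All statements are in the protocol article.

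- **Participant withdrawal criteria.** The list opens with "Participants will be withdrawn from the study" and its last trigger is "They have hematuria during treatment". Two neighboring triggers are graded: liver injury needs transaminases above 3 × ULN together with bilirubin above 2 × ULN, and pain must be unbearable and lead to cyst decompression. The hematuria trigger is not graded. The list also leaves room for discretion: "The principal investigator or co-investigators judge that they need to be withdrawn from the study".
- **Inclusion and exclusion criteria.** Hematuria does not appear. The only urinary exclusion is proteinuria above 1 g per day.
- **Measurement items and time points of data collection.** Cyst compression is described as a process "which is associated with pain, hypertension, hematuria, albuminuria, and loss of renal function". Table 2 schedules renal function and a urine test at every visit, including all six on-treatment visits from week 4 to week 24. The article does not say what the urine test measures.
- **Intervention.** Under basic therapy, "drugs used in the treatment of hypertension, hematuria, concurrent infections, and other diseases will be used reasonably for patients in both groups as basic therapy". Table 1 lists "Inhibit platelet aggregation and thrombosis" for one YNF ingredient and "Anti-coagulation and anti-thrombosis" for another.
- **Statistical analysis.** The primary analysis follows intention to treat, keeps everyone enrolled, and handles missing data by multiple imputation.

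**The concern.** The trial is sized on an eGFR difference at 24 weeks. A patient withdrawn from the study at, say, week 8 may have no eGFR after that point. Intention to treat keeps that patient in the analysis set, but the later values are then imputed and not observed.

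This matters more for hematuria than for an ordinary dropout reason. The trigger is an event after randomization that the product could plausibly influence, given the actions listed in Table 1. Blinding and 1:1 allocation do not make such withdrawals non-differential. It is also a foreseeable event in this population: the article expects hematuria to occur and provides treatment for it. A rule that ends follow-up at that point gives up primary-outcome data that the existing visit schedule would otherwise collect.

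**Working it through.** **1. The sections side by side.** Hematuria can be present at entry, is expected during the trial and is treated in both arms; if present during treatment, it ends study participation. No section keeps withdrawn patients on the eGFR schedule. The nearest text, under Data and safety monitoring, provides a recorded follow-up when the intervention is halted for an adverse event. In context that means following the event; it does not mention the scheduled eGFR visits.

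**2. The plan's own sample size.** Inputs from Sample size calculation: difference 6, SD 8.53, α = 0.05 (two-sided, per Statistical analysis), power 0.80, ratio 1:1.

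n per group = (1.96 + 0.8416)² × 8.53² × 2 / 6² = 7.849 × 72.76 × 2 / 36 = 31.7, so 32 per group and 64 in total. With 10% dropout, 64 / 0.90 = 71.1, so 72. The stated figures reproduce. The allowance is 72 − 64 = 8 patients, or 8/72 = 11.1%. The article does not say whether hematuria withdrawals are counted in it.

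**3. Illustration of arm imbalance.** No hematuria rate is given, so everything here except the arm size and the SD is assumed. Take 36 per arm, a fraction p withdrawn, and withdrawn patients' week-24 eGFR differing by d from that of patients who stay, with the same d in both arms. The mean of those who stay then differs from the mean of the whole arm by p × d, and the observed-case difference between arms shifts by (p₁ − p₀) × d. Let eight patients in all be withdrawn for hematuria, and let d run from 3 to 8.53 (one protocol SD).

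| Split | p₁ − p₀ | Shift at d = 3 | Shift at d = 8.53 |
|---|---|---|---|
| 4 v 4 | 0 | 0 | 0 |
| 5 v 3 | 2/36 | 0.17 | 0.47 |
| 6 v 2 | 4/36 | 0.33 | 0.95 |

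Against the planned difference of 6, the last row is 0.33/6 = 5.6% to 0.95/6 = 15.8%. These are observed-case shifts. Multiple imputation using the 4-weekly eGFR values may remove part of them.

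**4. Illustration of lost information.** If hematuria withdrawals come on top of the full 10% dropout and contribute no later information, the number left per arm is 36 × 0.90 × (1 − h), where h is the assumed share withdrawn for hematuria.

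| h | Left per arm | Power |
|---|---|---|
| 5% | 30.8 | 0.79 |
| 10% | 29.2 | 0.77 |
| 20% | 25.9 | 0.72 |
| 40% | 19.4 | 0.59 |

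If the 10% allowance already covers these patients, there is no added loss of planned sample size. The table is pessimistic in a second way, because it ignores eGFR values recorded before withdrawal.

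**The case against.** **The wording may already mean onset on treatment.** The trigger sits beside event-type triggers such as a serious adverse event or detected liver injury. A reader might infer that the rule certainly expels patients with stable hematuria at entry, or that it contradicts the Intervention section. Neither follows. The phrase can be read as hematuria arising on treatment, and a patient can be both treated and withdrawn. This objection stands, so the missing new-or-worse qualifier is a secondary matter of clarity.

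**It is a safety rule.** For a product credited with antiplatelet and anticoagulant actions, a strict bleeding rule is defensible, and whether a patient with stable hematuria should stay on drug is a clinical judgement. That stands too. It supports stopping the drug; it does not require ending eGFR measurement.

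**The loss of follow-up is not specific to hematuria.** Correct: it comes from the opening words shared by the whole list. Hematuria is the clearest case because the protocol itself expects it, but the remedy belongs to the shared wording.

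**The analysis already deals with it.** Intention to treat, multiple imputation, 4-weekly eGFR and a dropout allowance all help. They do so in part only, since imputed values depend on a model for what happens after withdrawal, while visits would supply the values themselves.

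**A condensed article may leave the details out.** A fuller protocol could define hematuria more narrowly or continue the visits. The text at hand, however, states a rule and states it without limit.

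**Differential loss is speculative.** The Discussion names diarrhea and increased urine output as the common adverse effects and does not mention bleeding. This limits what can be claimed about bias, as the conclusion reflects.

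**Conclusion.** The point holds in a limited form. As written, the rule can end eGFR follow-up before week 24 for a reason that may be related to treatment, and this undercuts an intention-to-treat analysis of the primary outcome. That conclusion rests on the text alone: withdrawal is from the study, and no section retains the visits.

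The size and direction of any bias cannot be determined from the documents. A reader might infer from Table 1 that YNF patients will be withdrawn more often, or from the illustrations that the result will be biased or the trial underpowered. The documents support neither inference. They give no hematuria rate, no rate by arm, and no eGFR gap between withdrawn and retained patients. The shifts of 0 to 0.95 and the power values of 0.59 to 0.79 show only what would follow from the stated assumptions.

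The change is worth making because it is specific, cheap and lowers a risk that the analysis can only partly repair.

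**What to change.** Amend the Participant withdrawal criteria so that hematuria on treatment leads to stopping study drug, while the scheduled eGFR visits continue to weeks 24 and 48 unless the patient withdraws consent. The same wording suits the other safety triggers in the list. Report hematuria stops by arm with the safety outcomes, naming hematuria explicitly: the list of possible safety events under Data and safety monitoring does not name it and would catch it only through the item for unexpected events attributed to the intervention.

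As a secondary clarification, consider limiting the trigger to hematuria that is new or clearly worse than at Visits 1 and 2, with stable hematuria managed as basic therapy. The investigators should decide this on safety grounds, since it would keep such patients on a product credited with antiplatelet and anticoagulant actions. The existing discretion to withdraw a patient should remain.

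Cost: a small amendment needing ethics approval (the article says each participating hospital's board approved the study), and visits for patients who are off drug. Those visits and urine tests are already scheduled. Trial status shows that screening ran from October 2018 to July 2019, so the change would reach patients already screened, and the sites should check that existing consent covers visits after study drug is stopped. The secondary clarification would also need baseline hematuria status on the case report form.
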